# Vitamin D supplementation in older people (VDOP): Study protocol for a randomised controlled intervention trial with monthly oral dosing with 12,000 IU, 24,000 IU or 48,000 IU of vitamin D_3_

**DOI:** 10.1186/1745-6215-14-299

**Published:** 2013-09-17

**Keywords:** Vitamin D supplementation trial, Bone mineral density, 25 hydroxy vitamin D, Parathyroid hormone, Bone markers, Older people

## Abstract

**Background:**

Vitamin D insufficiency is common in older people and may lead to secondary hyperparathyroidism, bone loss, impairment of muscle function and increased risk of falls and fractures. Vitamin D supplementation trials have yielded conflicting results with regard to decreasing rates of bone loss, falls and fractures and the optimal plasma concentration of 25 hydroxy vitamin D (25OHD) for skeletal health remains unclear.

**Method/design:**

Older (≥70 years) community dwelling men and women are recruited through General Practices in Northern England and 375 participants are randomised to take 12,000 international units (IU), 24,000 IU or 48,000 IU of vitamin D_3_ orally each month for one year starting in the winter or early spring. Hip BMD and anthropometry are measured at baseline and 12 months. Fasting blood samples are collected at baseline and three-month intervals for the measurement of plasma 25OHD, parathyroid hormone (PTH), biochemical markers of bone turnover and biochemistry to assess the dose–response and safety of supplementation. Questionnaire data include falls, fractures, quality of life, adverse events and outcomes, compliance, dietary calcium intake and sunshine exposure.

**Discussion:**

This is the first integrated vitamin D supplementation trial in older men and women using a range of doses given at monthly intervals to assess BMD, plasma 25OHD, PTH and biochemical markers of bone turnover and safety, quality of life and physical performance. We aim to investigate the vitamin D supplementation and plasma 25OHD concentration required to maintain bone health and to develop a set of biochemical markers that reflects the effect of vitamin D on bone. This will aid future studies investigating the effect of vitamin D supplementation on fracture risk.

#ISRCTN 35648481 (assigned 16 August 2012), EudraCT 2011-004890-10.

## Background

### Vitamin D status and musculoskeletal health

Vitamin D insufficiency is common in older people and may lead to increased bone resorption, bone loss, impairment of muscle function and an increased risk of falls and fractures. The results of clinical trials assessing the effect of vitamin D supplementation on bone loss, falls and fractures have yielded conflicting results and the blood concentration of 25 hydroxy vitamin D (25OHD) required to maintain optimal skeletal health remains unclear. Unfortunately, there is no universal consensus on the optimal way of assessing vitamin D status or on what constitutes vitamin D repletion at different ages throughout life [1].

Vitamin D status is currently assessed by measurement of plasma 25OHD concentration. In the UK, vitamin D deficiency has been defined as a plasma 25OHD less than 25 nmol/L, the upper end of the range at which vitamin D deficiency osteomalacia and rickets have been observed [2,3]. Recent epidemiological and cross-sectional studies have shown that 25OHD concentrations above 25 nmol/L may also be associated with secondary hyperparathyroidism, higher bone resorption, bone loss, impaired muscle function and a greater risk of falls and fragility fractures [4-8] when compared to concentrations of 40 to 75 nmol/L and above.

### Vitamin D status and requirements

A plasma 25OHD concentration of 40 to 50 nmol/L has been suggested as a cut-off for vitamin D insufficiency [2,9-11]. However, some experts have advocated higher concentrations of 25OHD (75 to 150 nmol/L) for the maintenance of bone health and other non-skeletal benefits [12-17]. Few individuals in the UK achieve these concentrations of 25OHD in winter and spring, when more than 80% of 45-year-old men and women have a plasma 25OHD concentration less than 75 nmol/L [18-20]. Vitamin D status is poorer in older people, where approximately 12% of people living in private households and 30% of care home residents have a plasma 25OHD concentration below 25 nmol/L throughout the year, reflecting their reduced exposure to sunlight, low dietary intake of vitamin D and potentially their higher expenditure of vitamin D [14,18,21].

The dietary Reference Nutrient Intake (RNI) for vitamin D in the UK for people over 65 years is currently 400 International Units (IU) (= 10 μg) per day. In the US, the Estimated Average Requirement (EAR) and Recommended Dietary Allowance (RDA) for those over 70 years of age is 600 (15 μg) and 800 IU (20 μg) per day, respectively [11,22]. It is recognised that supplementation is generally necessary to achieve these intakes [23]. Despite this advice, vitamin D supplementation is uncommon in older people, even in care home residents [18,24-26].

### Vitamin D supplementation and fracture risk

Several placebo-controlled intervention trials have examined the effect of vitamin D supplementation on fracture risk. Some meta-analyses suggest that vitamin D supplementation doses of 800 to 1000 IU daily decrease the incidence of falls and fractures in older women, whereas lower doses are ineffective [27-29]. In contrast, other meta-analyses, including the latest Cochrane Review [30], indicate that vitamin D supplementation does not decrease fracture risk, unless combined with calcium, when it reduces the risk of hip and other non-vertebral fractures in care home residents [31,32]. One randomised controlled trial of a single annual oral dose of 500,000 IU vitamin D showed an increase in falls and fractures, particularly in the first three months after administration [33]. Other studies using 300,000 or 600,000 IU per annum have shown mixed results: 100,000 IU administered at four-month intervals was associated with a decrease in fracture risk, whereas 300,000 IU of vitamin D_2_ by i.m. injection or 150,000 IU administered orally every three months was associated with no benefit [34-36]. These results suggest that not only the dose but also the frequency of administration may determine the risk and benefit for falls and fractures. The mechanisms of this association remain unclear and are likely to be multi-factorial.

The evidence for the effects of vitamin D supplementation on BMD or the prevention of bone loss in older people is conflicting [37,38]. The differences in the reported efficacy of vitamin D may be because the dose of vitamin D in several trials may have been too low or compliance and persistence with supplementation may have been poor, resulting in a failure to achieve a high enough plasma 25OHD to reduce bone loss and obtain an anti-fracture benefit [13,39-41]. Alternatively, the participants in some trials may have been vitamin D replete [41], even if their baseline plasma 25OHD concentrations were lower than those advocated by North American experts [12,15,16]. Moreover, differences in reported efficacy may have been due to differences in the study population, the dose of vitamin D, the route and frequency of administration and/or the use of different forms of vitamin D (vitamin D_2_ and vitamin D_3_).

Several studies have indicated that the achieved plasma 25OHD concentration, rather than the vitamin D dose given, predicts the effect on bone health [42]. However, measurement of plasma 25OHD, parathyroid hormone (PTH) and other potential markers of vitamin D status have only been performed in a small minority of participants in these intervention studies [41], limiting the ability to explore the relationship between plasma 25OHD concentrations achieved and bone loss and fracture prevention.

### Vitamin D status markers for bone health

Before performing further studies of the effect of vitamin D supplementation on the risk of major outcomes such as fragility fractures or cardiovascular disease [12,13,43,44], there is a need to understand better the relationship between vitamin D intake, plasma 25OHD and bone health in older people and to develop better functional markers of vitamin D status, reflecting vitamin D function at the level of the target organ [3,45]. These functional markers will be instrumental in establishing clearer criteria for vitamin D sufficiency and insufficiency and help to clarify the optimal dose and frequency of vitamin D supplementation. Potential markers of vitamin D status have been reviewed [3]. Plasma PTH has been proposed as a functional marker, because an elevated concentration is a recognised risk factor for bone loss and fractures in older people [6-9,13,46-48], which can potentially be modified by vitamin D supplementation [49,50]. The circulating concentration of 25OHD below which PTH increases outside the normal range may be used to establish a threshold value for vitamin D insufficiency [1]. However, PTH varies within and between people at any given concentration of 25OHD [18,51], as PTH depends on many factors other than vitamin D status [52]. These include stage of life, ethnic background, dietary calcium and phosphate intake, time of day, renal function, serum magnesium, physical inactivity and medication use [3,14,53-55].

### Aim

The Optimising Vitamin D Status in Older People (VDOP) trial aims to examine the relationship between vitamin D supplementation at a range of doses and the change in bone mineral density (BMD) in older people living in private households in the North East of England. Vitamin D_3_ supplementation is given orally each month, for a year (12,000 IU/month, 24,000 IU/month or 48,000 IU/month, equivalent to 400 IU/day, 800 IU/day and 1,600 IU/day, respectively). We will explore the relationship between the change in BMD and the achieved plasma 25OHD and PTH over 12 months. As BMD is the result of the balance between bone formation and resorption, the effect of the supplement on the change in markers of bone turnover will be explored. Plasma C-terminal telopeptide (CTX), bone specific alkaline phosphatase (bone ALP) and N-terminal propeptide of procollagen type I (P1NP) will be measured, as it has been suggested that these may be the best surrogate bone turnover markers for the effect of pharmacological intervention on fracture incidence [56]. We will also investigate the effect of duration of treatment and season on the dose–response.

### Rationale for dosage and dosing regimen

Two of the dosages applied in this trial correspond to the current Scientific Advisory Committee on Nutrition (SACN) RNI (400 IU/day) and the Institute of Medicine (IOM) RDA (800 IU/day) for this age group [2,11]. The highest dose is twice the IOM RDA and well below the IOM Tolerable Upper Intake Level (TUIL) defined by the IOM (4,000 IU/day) [11].

This trial uses a monthly dosage scheme as this is expected to result in improved compliance compared to daily or weekly dosages [57]. Compliance will be encouraged through administration of the dose under direct supervision on four occasions and taking the other doses will be prompted by telephone calls by staff from the research centre.

## Methods/design

### Study design

The VDOP trial is a single centre parallel group, randomised, double blind interventional trial testing the effects of three dosages of oral vitamin D_3_ given each month to men and women 70 years old and older for a year. The primary outcome is the change in BMD at the hip (total hip BMD) from baseline to 12 months post intervention.

### Recruitment

Community dwelling men and women 70-years-old and older, are recruited through General Practices (GP) in Tyneside, Wearside and Northumberland, participating in the Northern and Yorkshire Primary Care Research Network (PCRN-NY). Potentially eligible participants are identified from GP practice registers, after initial screening against inclusion and exclusion criteria on electronic medical records. An invitation letter is sent to potential participants, including details of the study and a pre-paid response slip. Those expressing an interest are contacted by the research team, further screening performed to ensure that the participant is eligible and an invitation to participate is then offered, after any discussions the potential participant might wish. If still interested, an appointment is made for the first study visit, when written informed consent is obtained, and a blood sample is collected to perform the final assessment of eligibility (screening for biochemical exclusion criteria: see below). If eligible, baseline visit measurements and questionnaires are completed.

### Inclusion criteria

Inclusion criteria are as follows:

1. Ambulatory, community dwelling men and women 70 years old and older

2. Individuals capable of giving informed consent on their own behalf

3. Individuals willing to attend the Study Centre (The Clinical Ageing Research Unit (CARU)) on six occasions and to be contacted by telephone at monthly intervals between study visits over twelve months

### Exclusion criteria

Exclusion criteria are as follows:

1. Current antiresorptive or anabolic treatment for osteoporosis

2. Treatment with bisphosphonates for osteoporosis in the past two years

3. Current supplement use of vitamin D (>400 IU/day) or calcium (>500 mg/day) (including use of over-the-counter preparations)

4. Fragility fracture in the previous six months

5. Known primary hyperparathyroidism

6. History of renal stones

7. Hip replacement

Biochemical:

1. Hypercalcaemia (albumin-adjusted serum calcium >2.60 mmol/L)

2. Renal impairment (Stage 4 or 5 Chronic Kidney Disease: estimated glomerular filtration rate (eGFR) below 30 ml/min/1.73m^2^ calculated using the modification of diet in renal disease (MDRD) formula.

There will be no limits to concomitant care or medication use other than defined in the inclusion and exclusion criteria. Participation in the VDOP trial is discontinued when during the course of the trial conditions develop where vitamin D supplementation is contra-indicated.

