### Measurements

An overview of the timing of measurements, sample collections and data collection is given in Table 1. Total hip BMD is measured using Dual-Energy X-ray Absorptiometry (DXA) (i-Lunar DXa, GE Healthcare, Madison Wisconsin USA) at baseline and 12 months. The densitometer is calibrated daily prior to participant scanning. The total radiation dose (0.04 mSv) is equivalent to having a chest X-ray. Height and weight, demispan, waist-hip ratio and the Timed Up and Go (TU&G) test are determined [58] and the participant’s medical history (including medication and supplement use) reviewed. A standardised physical exam including the assessment of vital signs, blood pressure, and questionnaires assessing bone pain, fracture risk and falls history are performed (adapted from standard clinical care questions and the Fracture Risk Assessment (FRAX) tool [59]). Blood and timed urine samples are collected after an overnight fast between 8:30 and 11:30 AM. After venipuncture, participants are offered breakfast. Questionnaires are used to collect data on demographics, quality of life (WHOQol-BREF UK version and UK WHOQOL-old; [60,61]), dietary calcium and vitamin D intake (adapted from Calquest; [62]) and sunshine exposure in the UK and during overseas travel (adapted from [63]). Participants are also asked to keep a three-month prospective falls diary. At each visit, information is collected on participant-reported adverse events (AEs), serious adverse events (SAEs) and suspected unexpected serious adverse reactions (SUSARs). In addition, at every visit, safety is assessed specifically by performing full blood count, serum albumin adjusted calcium, creatinine and liver function. Information on clinical fractures during the study is recorded as a safety measure.

**Table 1 T1:** Schedule of study procedures for VDOP

		**Phone call 0**	**Visit 0**	**Visit 1**	**Phone call 1**	**Phone call 2**	**Visit 2**	**Phone call 3**	**Phone call 4**	**Visit 3**	**Phone call 5**	**Phone call 6**	**Visit 4**	**Phone call 7**	**Phone call 8**	**Visit 5**
	Pre- Screening	Pre- Screening	Screening	Baseline visit	FUP^a^ 1	FUP^a^ 2	FUP^a^ 3	FUP^a^ 4	FUP^a^ 5	FUP^a^ 6	FUP^a^ 7	FUP^a^ 8	FUP^a^ 9	FUP^a^ 10	FUP^a^ 11	Final visit
Venue	PIC^a^	Home	CARU^a^	CARU^a^	Home	Home	CARU^a^	Home	Home	CARU^a^	Home	Home	CARU^a^	Home	Home	CARU^a^
Month	−1	0	0	**0**	1	2	**3**	4	5	**6**	7	8	**9**	10	11	**12**
Identification	X															
Pre-Screening		X														

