### Statistical analyses

The primary outcome of this study is the 12 month change in BMD at the hip (total hip BMD).

The secondary outcome measures are the changes in plasma 25OHD concentration and PTH, so as to explore their use as functional markers in relation to change in BMD and biochemical markers of bone turnover. Data are also being obtained on the proportion of participants in each treatment group who fall, the number of falls, quality of life and safety.

Analyses are performed according to a formal pre-planned documented analysis plan. Analysis will be carried out primarily on an intention-to-treat basis although other exploratory analyses may also be considered. There are no planned interim analyses.

Data with missing observations due to loss to follow-up will be examined to determine both the extent of missingness and whether it is missing at random or is selective. If data are missing to a sufficient extent, the use of appropriate multiple imputation techniques will be considered to allow for this in the analysis.

Analysis of the primary outcome measure (12 month change in BMD at the hip) will be performed using Analysis of Covariance (ANCOVA) to compare the response in the three treatment groups while allowing for the effects of covariates. Baseline BMD at the hip, PTH and 25OHD measures will be included in addition to measures of kidney function, BMI, gender and age. Interactions will also be explored. The inclusion of baseline values as covariates will also enable the examination of possible interactions between effects observed and these values.

A number of secondary analyses will also be undertaken. Alternative clinical indicators (such as change in plasma 25OHD, PTH, falls, physical performance, quality of life measures and other biochemical markers) will be compared between the three treatment groups, using similar techniques to those described above.

The relationship of PTH as a dependent variable with 25OHD and kidney function as independent variables will be examined using regression methods. Further exploratory regression models will explore the relationships of 25OHD and PTH with change in BMD and biochemical markers of bone turnover. The relationship between 25OHD and BMI will also be explored using similar regression methods.

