### Ethical considerations

This study has received a favourable opinion from the Sunderland Research Ethics Committee (REC, 12/NE/0050) and R and D approval from the Newcastle upon Tyne Hospitals NHS Foundation Trust (sponsor)*.* The conduct of this study is in accordance with the recommendations for physicians involved in research on human subjects adopted by the 18th World Medical Assembly, Helsinki 1964 and later revisions.

The study involves procedures that may be unfamiliar to participants and are not part of their standard medical care. These procedures are explained in information sheets provided to all potential participants prior to their screening visit and written informed consent is obtained prior to any study procedures. The consent form specifies the separate study components and includes an opt in/opt out section for genetic analyses and permission to be approached for potential affiliated studies. Participants who lack capacity to consent for themselves are excluded from this study. In the unlikely event that a participant loses capacity after they have provided consent to take part, their case will be reviewed by the Chief Investigator and the legal representative of the participant to decide whether to continue in the study.

The hip BMD DXA measurement involves a low dose of radiation (see measurements).

The latest Cochrane Review suggests that vitamin D supplementation may be associated with a small increased risk of gastrointestinal side effects, hypercalcaemia, renal stones and renal impairment, particularly when given with additional calcium or when active metabolites of vitamin D are used [32]. However, the doses to be used in this study are not generally associated with adverse events [11,22]. As we are using vitamin D alone, without additional calcium supplementation, we do not anticipate that this will pose a significant risk to participants. The highest dose of vitamin D_3_ used in this study is less than half the TUIL recently advised by the IOM [11,22].

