## Discussion and potential impact

This study will provide clarification of the dose of vitamin D required to prevent bone loss in older people in the UK and will influence the formulation of dietary recommendations of vitamin D at the population level. This study is novel and clinically relevant, as it will compare the effect of three different doses of vitamin D on BMD and plasma 25OHD, PTH and biochemical markers of bone turnover in both men and women. This study evaluates the effects of vitamin D as mono-therapy rather than combined with calcium. The data complement current evidence on the balance of risks in using vitamin D with or without calcium supplementation [68]. The study also offers the opportunity to evaluate the impact of different dosages of vitamin D supplement on structural (DXA Scanning) and biochemical markers which allow a better definition of Vitamin D sufficiency for bone health and to determine an adequate vitamin D intake to maintain musculoskeletal function. We aim to develop a set of biochemical markers that reflect the effect of vitamin D intervention on bone. This will aid future larger studies investigating the effect of vitamin D supplementation on fracture risk.

Although the study is primarily powered to detect an effect of vitamin D supplementation on BMD, it will also provide data on the effect of vitamin D supplementation on other functional outcomes, such as quality of life, physical performance and falls. Further, safety data are collected and analysed for the effects of the different dosages, temporal trends and the cumulative dosage. In addition, this study will provide data on the effect of season on vitamin D status and other markers and improve knowledge of the role of monthly (rather than daily) dosing with vitamin D.

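### A contra-indication ends participation in the trial, not just the supplement, so the only follow-up hip BMD and later falls and safety data would be lost

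*Protocol article*

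**What the plan says.** The rule closes the Exclusion criteria section: "Participation in the VDOP trial is discontinued when during the course of the trial conditions develop where vitamin D supplementation is contra-indicated". What stops is participation in the trial. The Exit strategy section uses narrower wording when it means that only the supplement ends. No section describes follow-up off supplement or an early scan for those who stop.

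The Study design section sets the endpoint: "The primary outcome is the change in BMD at the hip (total hip BMD) from baseline to 12 months post intervention". The Abstract gives the timing: "Hip BMD and anthropometry are measured at baseline and 12 months". Table 1 agrees, with DXA only at the baseline and final visits.

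On falls, the Measurements section says: "Participants are also asked to keep a three-month prospective falls diary". It also places blood count, adjusted calcium, creatinine and liver function at every visit.

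The Statistical analyses section says: "Analysis will be carried out primarily on an intention-to-treat basis". It will examine whether missingness is selective and, if enough is missing, "the use of appropriate multiple imputation techniques will be considered".

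Ethical considerations lists hypercalcaemia, renal stones and renal impairment among possible effects of vitamin D, but adds that "the doses to be used in this study are not generally associated with adverse events". The Discussion states that "safety data are collected and analysed for the effects of the different dosages, temporal trends and the cumulative dosage".

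**The concern.** Stopping a supplement that has become contra-indicated is right clinically. Ending the participant's follow-up does not follow from it. An intention-to-treat comparison needs the 12-month outcome of everyone randomised, whether or not they are still dosing. Here the protocol's own rule creates a missing outcome in someone who could have been scanned.

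The gap may also be informative. The protocol does not list the contra-indications. The natural candidates are hypercalcaemia, renal stones and stage 4–5 kidney disease, which are all grounds for exclusion at entry and overlap with the possible effects of vitamin D in Ethical considerations. Calcium and creatinine are checked at every visit, so the trial actively looks for two of them. If removals differ by arm, and those removed differ in bone loss, the contrast among completers is biased. Standard multiple imputation assumes data are missing at random, which this reason for leaving may breach.

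The safety comparison is affected more directly. Scheduled observation would stop just after a possible harm, so recovery or progression after stopping the product would not be recorded at trial visits.

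**Working it through.** **1. The plan's own figures reproduce.** The inputs from Sample size and power calculation are SD 0.015, difference 0.006 g/cm², two-sided alpha 0.05 and power 80%.

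- Normal approximation: n = 2 × (1.960 + 0.842)² × (0.015/0.006)² = 98.1, so 99 per arm. The t-test version gives 99.08, so 100, as stated.
- Attrition: 100/(1 − 0.20) = 125 per arm, 375 in total, as stated.
- Standard error of a pairwise contrast with 100 evaluable per arm: 0.015 × √(2/100) = 0.0021 g/cm².

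**2. What a removed participant contributes.** There are two BMD measurements, at months 0 and 12. Removal at any time between them leaves no post-baseline value, so there is no intermediate BMD from which to impute.

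**3. Size of bias in a completers' contrast.** In one arm, let p be the proportion removed and d the amount by which the removed participants' mean 12-month change falls short of the completers'. The completers' mean then exceeds the full-arm mean by p × d. The bias in a contrast is p₁d₁ − p₂d₂, which becomes (p₁ − p₂) × d when d is the same in both arms. The document gives neither p nor d, so every row below is an assumption.

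| Removed, arm v arm | Shortfall d | Bias (g/cm²) | Share of 0.006 | In SEs |
|---|---|---|---|---|
| 2% v 2% | 0.5 SD = 0.0075 | 0 | 0 | 0 |
| 0% v 2% | 0.0075 | 0.02 × 0.0075 = 0.00015 | 2.5% | 0.07 |
| 2% v 5% | 0.0075 | 0.03 × 0.0075 = 0.000225 | 3.75% | 0.11 |
| 2% v 8% | 1 SD = 0.015 | 0.06 × 0.015 = 0.0009 | 15% | 0.42 |
| 0% v 10% (extreme) | 0.015 | 0.10 × 0.015 = 0.0015 | 25% | 0.71 |

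Of 125 participants, 2% is two or three people. The sign reverses if those removed would have lost less bone than the completers.

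**4. Power.** If 1%, 2% or 5% per arm were lost on top of the 20% already allowed, 98, 97 or 93 per arm would remain. Power for 0.006 g/cm² would then be 80.0%, 79.6% or 77.9% (normal approximation). Precision is not the issue.

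**The case against.** The strongest reply is that this is a literal reading of one sentence in a condensed article. The authors may have meant only that dosing stops, and detailed rules for visits after discontinuation usually sit in the full protocol. That may be so, but the article states a rule here; it does not merely leave one out. It uses different wording elsewhere when it means the supplement alone. If dosing was what was meant, the sentence says the wrong thing and needs the same correction.

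The second reply is that the plan already copes: 20% attrition is budgeted, selective missingness will be examined, imputation may be used, the ANCOVA adjusts for kidney function and other covariates, and three-monthly 25OHD, PTH and bone markers from before removal could inform the imputation. This stands as far as feasibility and power go. It does not replace an outcome that could have been measured.

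The third reply is that events should be few and need not differ by arm. All arms receive vitamin D, the highest dose is below half the cited upper limit, no calcium is given, people at obvious risk are excluded, and no dose gradient is stated. This stands, and it favours the low end of the table. Even there, the assumed 0.5 SD shortfall exceeds the 0.4 SD effect the trial is powered for, so 2.5% may itself be generous.

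Lastly, the triggering harm is not lost. Adverse events are recorded at visits, checked against medical records and assessed for causality. That also stands: what goes missing is the scheduled observation afterwards.

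**Conclusion.** The concern holds as a statement about the text. Followed as written, the rule removes the only post-baseline hip BMD, and the later falls and safety data, for reasons that may be related to treatment. That conflicts with the stated intention-to-treat aim.

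Its effect on the primary comparison is probably small. The more plausible scenarios give 0 to about 4% of the 0.006 g/cm² target, and reaching 25% takes an extreme combination that nothing in the document supports. These figures rest on assumed removal rates and an assumed difference in bone loss. The number affected, any imbalance between arms and the direction of bias cannot be established from the document. The stronger reason to act is that the trial intends to compare safety by dose and over time. This is a point to consider, held with medium confidence because the authors may have intended the narrower meaning.

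**What to change.** Keep the clinical stopping rule but apply it to the investigational product alone. Suggested wording:

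> The IMP is stopped if a condition develops in which vitamin D is contra-indicated. Unless consent is withdrawn, the participant continues with scheduled visits, falls diaries, bloods and the 12-month DXA, and is analysed in the randomised arm. The date and reason for stopping are recorded.

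This takes a one-sentence amendment. The visits and final DXA are already in Table 1, so no new assessment is needed. The cost is the small burden, on participants and staff, of following a few people who are no longer taking the supplement.
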